# Functional gait rehabilitation in elderly people following a fall-related hip fracture using a treadmill with visual context: design of a randomized controlled trial

**DOI:** 10.1186/1471-2318-13-34

**Published:** 2013-04-16

**Keywords:** Gait adaptability, Falling, Older adults, Hip fracture, Treadmill, Exercise

## Abstract

**Background:**

Walking requires gait adjustments in order to walk safely in continually changing environments. Gait adaptability is reduced in older adults, and (near) falls, fall-related hip fractures and fear of falling are common in this population. Most falls occur due to inaccurate foot placement relative to environmental hazards, such as obstacles. The C-Mill is an innovative, instrumented treadmill on which visual context (e.g., obstacles) is projected. The C-Mill is well suited to train foot positioning relative to environmental properties while concurrently utilizing the high-intensity practice benefits associated with conventional treadmill training. The present protocol was designed to examine the efficacy of C-Mill gait adaptability treadmill training for improving walking ability and reducing fall incidence and fear of falling relative to conventional treadmill training and usual care. We hypothesize that C-Mill gait adaptability treadmill training and conventional treadmill training result in better walking ability than usual care due to the enhanced training intensity, with superior effects for C-Mill gait adaptability treadmill training on gait adaptability aspects of walking given the concurrent focus on practicing step adjustments.

**Methods/design:**

The protocol describes a parallel group, single-blind, superiority randomized controlled trial with pre-tests, post-tests, retention-tests and follow-up. Hundred-twenty-six older adults with a recent fall-related hip fracture will be recruited from inpatient rehabilitation care and allocated to six weeks of C-Mill gait adaptability treadmill training (high-intensity, adaptive stepping), conventional treadmill training (high-intensity, repetitive stepping) or usual care physical therapy using block randomization, with allocation concealment by opaque sequentially numbered envelopes. Only data collectors are blind to group allocation. Study parameters related to walking ability will be assessed as primary outcome pre-training, post-training, after 4 weeks retention and 12 months follow-up. Secondary study parameters are measures related to fall incidence, fear of falling and general health.

**Discussion:**

The study will shed light on the relative importance of adaptive versus repetitive stepping and practice intensity for effective intervention programs directed at improving walking ability and reducing fall risk and fear of falling in older adults with a recent fall-related hip fracture, which may help reduce future fall-related health-care costs.

**Trial registration:**

The Netherlands Trial Register (http://NTR3222).

## Background

Falls among older adults are a growing public health problem, particularly in western society with its increasingly aging population. Approximately one third of all community-living people over 65 years fall each year [1-5], and fall incidence rises even further with age [2-6]. Fall incidence is substantially higher in older adults residing in nursing, rehabilitation and hospital care facilities, especially after an injurious fall [6-9]. Falls may lead to fractures, soft tissue injuries and even death [6,10-12]. In The Netherlands, falls among older adults yearly result in 83000 emergency room treatments, 43000 hospital admissions and 2165 deaths [13], which entails an estimated yearly cost of 820M euro [13]. Furthermore, falls are associated with reduced participation, reduced functional ability and fear of falling [6,10,12].

Falls are thus common in older adults and their consequences and costs are well documented. Falls in older adults mostly occur during walking [9,11] and are caused by a combination of intrinsic and extrinsic factors. Intrinsic factors associated with falling are generally age-related and include reduced executive function, increased gait-related attentional demands, decreased muscle strength, impaired vision, and gait and balance impairments [1,14-20]. Extrinsic risk factors for falling include poor lighting conditions, inappropriate footwear and environmental hazards such as obstacles, cluttered terrain, the presence of pets and slippery surfaces [1,6,11]. These environmental hazards contribute to approximately half of all falls [1,6,11,21,22]. Therefore, gait adaptability (i.e., the ability to adjust gait to environmental hazards; [23]) evidently seems an important factor to include in intervention programs aimed at reducing falls in older adults.

Strikingly, however, intervention programs rarely incorporate gait adaptability as an explicit target to reduce falls and fall risk in older adults (see Weerdesteyn et al. [24] for a notable exception), despite its self-evident importance. Instead, fall-prevention programs have focused on other factors, including vitamin D supplementation, medication optimisation, education, multi-factorial interventions, environmental home safety interventions and exercise programs [5]. Although multi-factorial interventions appear effective in reducing fall rate, beneficial effects for reducing fall risk as well as fall rate in community dwelling older adults are only established for exercise programs and environmental home safety interventions [5]. The removal of environmental hazards in the house is thus an effective form of fall prevention, which further adds to the importance of environmental hazards as risk factor for falls, and highlights the need for exercise programs that integrate the environmental hazards encountered in every-day life (i.e., gait adaptability).

The fact that gait adaptability is generally not targeted in interventions aimed at reducing falls and fall risk in older adults implies that there is ample room for improvement of fall-prevention programs. The recent introduction of the C-Mill (Figure 1; ForceLink, Culemborg, The Netherlands) holds significant promise in that regard. The C-Mill is an innovative, instrumented rehabilitation treadmill with task-relevant visual context (e.g., obstacles, stepping targets) projected on the belt’s surface. The C-Mill was explicitly developed as a therapeutic tool to practice gait adaptability, elicited by aligning foot placement relative to the projected visual context [25]. In other words, the presented obstacles and stepping targets on the belt’s surface mandate gait adjustments to accurately position the feet relative to that visual context, akin to the gait adjustments required to walk safely in continually changing everyday environments. Because the C-Mill is instrumented with a force platform, it is known when and where the feet are placed on the belt’s surface [26], allowing for direct performance feedback with regard to gait parameters (e.g., step width, step length) as well as gait-context interactions (e.g., foot placement relative to the presented visual context; see Methods for more details). Whereas C-Mill training is focused explicitly on practicing gait adaptability relative to environmental hazards, it may as well implicitly target various intrinsic and extrinsic factors associated with falling, such as executive function [14,17,27], gait-related attentional demands [17,27-29], postural control during walking and step adjustments [30,31], and muscle strength [31-33].

**Figure 1 F1:**
[figure not shown]
**C-Mill.** The C-Mill is a 3-m long instrumented treadmill with visual objects such as stepping targets and obstacles projected on the belt to facilitate practice of foot placement relative to environmental context. A force platform is embedded in the treadmill for real-time determination of gait and foot-placement positions, allowing for various gait adaptability interventions accustomed to an individual’s gait. The visual context is projected on the belt’s surface, approaching the patient with the speed of the treadmill belt. The handrails permit weight-bearing and allow early training in a safe environment.

This study protocol is designed to examine the efficacy of C-Mill gait adaptability training for improving walking ability and reducing fall incidence and fear of falling in older adults residing in inpatient rehabilitation care to recover from a fall-related hip fracture, a group particularly prone to falling [6-9]. The efficacy of C-Mill gait adaptability training will not only be contrasted against usual care, comprising of exercises in strength, balance, overground walking, transfers and activities of daily living, but also against intensity matched conventional treadmill training (i.e., without visual context presented on the belt), promoting repetitive stepping. Literature on conventional treadmill training in older adults recovering from hip injury is quite scarce, but generally positive with regard to its efficacy [32,33]. Conventional treadmill training outperforms overground gait training in that regard, most likely because of the enhanced intensity of training (i.e., defined in number of steps taken per training session). Older adults with a total hip arthroplasty, for example, performed 1000-1500 steps during a conventional treadmill training session compared to 100-150 steps during an overground gait training session of similar duration [32]. We therefore hypothesize that both conventional treadmill training and C-Mill gait adaptability treadmill training result in better outcomes related to walking ability than usual care due to the enhanced training intensity, with superior effects for C-Mill gait adaptability treadmill training on gait adaptability aspects of walking given the concurrent focus on practicing gait adaptability. The present study will thus shed light on the relative importance of high versus low practice intensity and adaptive versus repetitive stepping as key ingredients for effective intervention programs aimed at improving walking ability and reducing fall risk and fear of falling in older adults recovering from a fall-related hip fracture.

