### Intervention program

The intervention programs will be dose-matched in terms of duration (i.e., 40 minutes per session) and frequency (i.e., five sessions per week) of therapy over a 6-week inpatient intervention period. All intervention programs will be provided by physical therapists of Solis Zorggroep, Deventer, The Netherlands. Therapy sessions will typically be conducted by a single physical therapist with two participants per session; the two participants alternately exercise and rest, resulting in 20 minutes of practice per session. Physical therapists and participants cannot be blinded to group allocation.

In the *usual care* (UC) control group, participants will receive conventional physical therapy in all 30 sessions, consisting of exercises of upper-leg strength, balance, transfers, overground walking, and activities of daily living, following locally implemented guidelines of Solis Zorggroep, Deventer, The Netherlands and Deventer Hospital, Deventer, The Netherlands regarding the treatment of hip fractures.

In the *conventional treadmill* (CT) intervention group, participants will receive 15 conventional physical therapy sessions (as in UC) and 15 conventional treadmill training sessions (week 1-3: 2 per week, week 4-6: 3 per week) with an emphasis on repetitive stepping. Participants will walk at comfortable treadmill walking speed, without body-weight support other than handrail support. Comfortable treadmill walking speed will be determined at the beginning of each session in order to promote the quality and safety of walking as appraised by the physical therapist. The initial focus of conventional treadmill training will be on the quality and safety aspects of walking: therefore, therapists may give instructions regarding the walking pattern. After a safe walking pattern has been established, the focus will gradually shift towards walking faster and longer. Participants in the CT group will walk on the C-Mill treadmill (C-Mill, ForceLink, Culemborg, The Netherlands), but without projection of visual context on the belt’s surface.

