In the *adaptability treadmill* (AT) intervention group, participants will receive 15 conventional physical therapy sessions (as in UC) and 15 C-Mill gait adaptability treadmill training sessions (week 1-3: 2 per week, week 4-6: 3 per week) with an emphasis on practicing gait adaptability. As in CT, participants will walk at comfortable treadmill walking speed, without body-weight support other than handrail support. The two AT training sessions in the first week will consist of conventional treadmill training with an emphasis on the safety and quality aspects of walking (i.e., without visual context, similar to CT), so that participants will become acquainted to treadmill walking.

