## Conclusions

The study will provide insight into the effect of C-Mill gait adaptability treadmill training and conventional treadmill training for improving walking ability and reducing fall risk and fear of falling in older adults recovering from a fall-related hip fracture. In this regard, the results of this study are likely to contribute to the effectiveness of intervention programs. Moreover, the study will shed light on the relative importance of adaptive versus repetitive stepping and high versus low intensity of practice as ingredients for fall prevention programs, and may help reduce future fall-related health-care costs. The results of this study are expected in 2015.

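### The treadmill-versus-usual-care contrasts estimate the effect of swapping half the conventional sessions for treadmill sessions, which cannot be credited to practice intensity

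*Protocol article*

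**What the plan says.** **The claim about intensity.** The Background, like the Abstract, expects both treadmill programmes to "result in better outcomes related to walking ability than usual care due to the enhanced training intensity". Intensity is defined there as the number of steps in a session. The supporting evidence is a cited study of people with a hip arthroplasty, who "performed 1000-1500 steps during a conventional treadmill training session compared to 100-150 steps during an overground gait training session of similar duration". The Background then says the trial will inform on the "relative importance of high versus low practice intensity and adaptive versus repetitive stepping as key ingredients for effective intervention programs". The Abstract's Discussion makes a similar promise, and the Conclusions name "high versus low intensity of practice as ingredients for fall prevention programs" among the things the study will illuminate.

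**The arms (Intervention program).**
- UC: "participants will receive conventional physical therapy in all 30 sessions, consisting of exercises of upper-leg strength, balance, transfers, overground walking, and activities of daily living".
- CT: "participants will receive 15 conventional physical therapy sessions (as in UC) and 15 conventional treadmill training sessions".
- AT: "participants will receive 15 conventional physical therapy sessions (as in UC) and 15 C-Mill gait adaptability treadmill training sessions".

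All three programmes have the same session length and frequency over six weeks. Two participants typically share a session and take turns, which leaves 20 minutes of practice each. CT and AT participants walk on the treadmill with no body-weight support apart from the handrails.

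**The planned check.** The same section compares steps per session among groups and has therapists register the content of every individual session. The Limitations do not mention that therapy content differs between UC and the treadmill arms.

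**The concern.** The hypothesis names a cause: the treadmill arms are expected to do better than UC because participants take more steps. For CT versus UC to show that, the arms would have to differ in step dose and in little else that bears on the outcome. They differ in at least three respects: step dose, mode of walking (treadmill with handrail rather than overground), and the amount of conventional therapy received.

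The conventional sessions contain balance, transfer and daily-living practice, and the primary walking-ability measures include the POMA, the Elderly Mobility Scale and the Nottingham Extended Activities of Daily Living scale. The displaced content could therefore matter to the outcomes. A positive CT–UC result might come from steps, from mode, or from the change in content. A null result might mean that steps do not matter, or that a gain from steps was offset by the therapy given up. At stake is the conclusion on one of the two ingredient questions that the article puts forward.

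**Working it through.** **Inputs (all from Intervention program unless stated).** Five sessions a week for 6 weeks; treadmill sessions 2 a week in weeks 1–3 and 3 a week in weeks 4–6; 20 minutes of practice per session; no projected context in the two AT treadmill sessions of week 1. Steps per session come from the cited study in the Background.

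**1. The plan's session counts reproduce.**
- Total sessions: 5 × 6 = 30.
- Treadmill sessions in CT and AT: 3 × 2 + 3 × 3 = 15, as stated.
- Conventional sessions left in CT and AT: 30 − 15 = 15, as stated.

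**2. Conventional practice time.**
- UC: 30 × 20 = 600 minutes.
- CT and AT: 15 × 20 = 300 minutes, a ratio of 0.5.

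**3. Step dose, for illustration.** Assume the cited study's figures apply and that every conventional session is entirely overground walking, the case most favourable to UC.
- UC: 30 × 100 = 3,000 to 30 × 150 = 4,500 steps.
- CT: 15 × 1,000 + 15 × 100 = 16,500 to 15 × 1,500 + 15 × 150 = 24,750 steps.
- Ratio: 16,500 / 3,000 = 24,750 / 4,500 = 5.5.

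A large difference in step dose is therefore plausible. The question is whether its effect can be isolated.

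**4. What the three arms can identify.** Take a simple additive description, used only to show the structure: arm mean = μ + τT + γC + αA. T is the number of treadmill sessions, C the number of conventional sessions, and A the number of AT sessions with projected context (15 − 2 = 13).

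| Arm | T | C | A |
|---|---|---|---|
| UC | 0 | 30 | 0 |
| CT | 15 | 15 | 0 |
| AT | 15 | 15 | 13 |

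The contrasts are:
- CT − UC = 15τ − 15γ = 15(τ − γ)
- AT − UC = 15(τ − γ) + 13α
- AT − CT = 13α

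T + C = 30 in every arm, so the four columns (intercept, T, C, A) have rank 3. Only the difference τ − γ is estimable, that is, a treadmill session compared with the conventional session it replaces. A zero CT–UC difference means τ = γ; it does not mean τ = 0. In addition, τ already bundles step count with treadmill mode and handrail support. AT − CT is free of γ, because conventional content is equal in the two arms.

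**5. What the step-count comparison adds.** It tests whether steps per session differ between UC and the treadmill arms, and whether AT and CT are alike. It does not alter the table above, so it cannot separate τ from γ.

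**The case against.** The strongest reply is that substitution is deliberate and openly described. At fixed therapy time, more treadmill steps must displace something, and adding treadmill sessions on top would confound intensity with total therapy time. Equal-time substitution is a defensible trade-off. This stands, and the design is not faulted. It also determines what the contrast means: a replacement effect.

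It can also be said that the formal aim is the efficacy of C-Mill training, that the language about ingredients is tentative, and that no test or sample-size input depends on attributing CT–UC to intensity. This is correct as to the analysis. The hypothesis in the Abstract and Background is nevertheless causal in wording, and the relative importance of intensity is promised repeatedly.

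Four stronger readings might be inferred, and the document does not support them:
- *The lack of a low-intensity adaptive arm prevents the adaptability effect from being estimated.* That absence prevents an interaction from being estimated. AT versus CT still addresses adaptive versus repetitive stepping, because both arms have 15 + 15 sessions and are planned as intensity matched.
- *The treadmill arms lose half of all other therapy content.* Half is exact for conventional sessions. Those sessions include overground walking, and the content mix is not given, so the loss of any one exercise type is unknown.
- *The Conclusions attribute a difference to intensity.* They only name intensity as something the study will inform on. The causal wording is in the Abstract and Background, which also credit adaptive practice for AT's expected advantage in gait adaptability.
- *The comparisons with UC are biased.* As estimates of the substitution they are valid, and any distortion of the intensity interpretation has no known direction.

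**Conclusion.** The point holds as a limit on interpretation. CT–UC and AT–UC validly estimate the effect of replacing 15 of 30 conventional sessions, about 300 of 600 practice minutes, with treadmill or adaptive treadmill sessions at equal therapy time. They do not identify the effect of high versus low intensity, whichever way the result falls, and so cannot support a statement of how important intensity is relative to adaptability. AT–CT does support the adaptive-versus-repetitive question.

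The session counts are exact. The minutes rest on the typical arrangement of two participants per session. The algebra in the working assumes additive session effects, but the collinearity behind it follows from the schedule alone. The document gives no figure from which to size the effect on any outcome, and none is claimed. The sample size is unaffected, since its inputs (3.5 and 4.8 POMA points, correlation 0.7, alpha 0.017) do not involve intensity. The wording should be corrected, because it governs what the trial may conclude on one of its two ingredient questions.

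**What to change.** 1. State CT–UC and AT–UC in the objectives, hypothesis and conclusions as the effect of replacing half of the usual physical therapy sessions with treadmill training (adaptive, for AT) at equal therapy time.
2. Reserve the ingredient claim for AT–CT, as adaptive versus repetitive stepping.
3. Drop the statements that a benefit over UC is due to intensity and that the trial shows intensity's relative importance, or label them as interpretation not supported by randomisation.
4. Add to the Limitations that step dose, walking mode with handrail support, and conventional-therapy content change together between UC and the treadmill arms.
5. Report the registered session content for each arm beside the step counts, so that readers can see what was displaced.

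The cost is some rewording, one descriptive table from records that therapists already keep, and a narrower claim. No change to the arms or to the treatment schedule is proposed.

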## Methods/design

### Recruitment

All patients with a hip fracture admitted to residential and rehabilitation centre Zorggroep Solis, Deventer, The Netherlands will be assessed for eligibility within 3 days from admission by a physical therapist during regular intake. We aim to recruit 126 geriatric patients. Inclusion criteria are admission with a hip fracture related to falling, age ≥ 65 years, Functional Ambulation Category score 2 or higher (FAC, [34,35]), expected duration of admission ≥ 6 weeks and an ability to understand and execute simple instructions. Exclusion criteria are not being allowed to bear weight on the affected leg, moderate or severe cognitive impairments as indicated with a score below 18 at the Mini-Mental State Examination (MMSE, [36]), severe non-corrected visual impairments, contraindication to physical activity and an activity tolerance below 40 minutes with rest intervals. Patients eligible for participation will be informed of the current study by the physical therapist, both verbally and in writing. Patients who are willing to participate will be asked to give informed consent.

